**Figure 3 fig3:**
[figure not shown]
Timeline of included subjects. ADEs, adverse drug events; ADWEs, adverse drug withdrawal events; PROMs, patient-reported outcome measures.

In both intervention and control phase, ADEs/ADWEs will be identified by research staff based on a retrospective review of medical records from enrolment to index hospital discharge, or 30 days post recruitment, whatever comes first (post-intervention assessment). We will apply systematic trigger tools suggestive of ADEs/ADWEs occurrence (see Table 2). In detail, the final list is derived from the integration of different validated trigger tools that have been previously used in similar populations. The list was reviewed and validated by geriatricians and pharmacists within the research team (30–32).

**Table 2 tab2:** List of possible “alerts” for ADEs/ADWEs.

Type	Alert
Care alerts	Transfusion or use of blood products
	Code / arrest / rapid response team
	Acute dialysis / Acute kidney injury
	X-ray or Doppler studies for embolism or deep vein thrombosis
	Patient fall
	Immobilization
	In-hospital stroke
	Constipation
	Hypotension
	Lethargy
	Rash
	Unspecified adverse event
	Symptomatic bradycardia
	Delirium
Antidots and treatments	Vitamin K administration
	Antihistamines use
	Flumazenil use
	Naloxone use
	Antiemetic administration (for acute dyspepsia / nausea / vomiting)
	Haloperidol use
	Abrupt medication stop
Medication levels	Digoxin levels >2 ng/mL
	Carbamazepine levels >13 mcg/ml
Laboratory tests	Clostridioides difficile – positive stool
	Serum glucose <50 mg/dL
	Serum glucose >110 mg/dL
	INR > 5
	Haemoglobin or haematocrit decrease >25% / Acute bleeding
	Rising blood urea nitrogen or serum creatinine >2 times baseline
	Estimated glomerular filtration rate <35 mL/min/1.73 m2
	K > 6.0 mEq/L
	K < 2.9 mEq/L
	Na < 130 mEq/L
	ALT >80 U/L and/or AST > 84 U/L
	ALP > 350 U/L and/or total bilirubin >4 mg/dL
	CPK > 269 U/L
	TSH < 0.34 μUI/L or fT4 > 12 μg/dL
	White blood cells <3,000/μl
Emergency department	Emergency department visit within 48 h
	Time in emergency department >6 h
	Readmission within 30 days

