In detail, we will evaluate alert diagnoses: unexpected clinical manifestations occurring during the admission and that might be related or unrelated to the use (or lack of use) of a certain medication. We will also evaluate previously defined altered laboratory tests, according to reference laboratory and literature review. Finally, we will evaluate alert drugs: medications known to be used to correct an alteration produced by a first medication (e.g., naloxone to reverse opioid overdose). All triggers will be further reviewed to discern if they are clearly independent from clinical manifestations related to the patients’ condition. Causality will be then assessed using the 10-point Naranjo Scale (33). The severity of the event will be classified using a modified Hartwig and Siegel scale (34), ranging from trivial (event does not require additional treatment and as no sequalae) to fatal. Avoidability of the event will be assessed using a modified Schumock and Thornton questionnaire (35). Each potential ADE/ADWE form will be evaluated by the blinded members of the ADE/ADWE Adjudication Committee, consisting of a geriatrician and a clinical pharmacist not directly involved in the retrospective review process. In the case of disagreement, additional review by another blinded geriatrician/clinical pharmacist pair of evaluators will be requested. Also, 90 days post-discharge (post-discharge assessment), both experimental and control phase participants will be re-evaluated for quantitative polypharmacy, PROMs, unplanned health care utilization (acute hospital admission, emergency claims), and mortality.

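### The thyroid laboratory alert in Table 2 is wrong as printed: the TSH unit is 1,000-fold off, and the T4 limit does not fit free T4

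*Protocol article*

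**What the plan says.** Under Participant timeline and data collection, the protocol article describes a retrospective chart review in both phases: "We will apply systematic trigger tools suggestive of ADEs/ADWEs occurrence". The review window runs "from enrolment to index hospital discharge, or 30 days post recruitment, whatever comes first". The alerts are listed in Table 2, and the text says that they combine several validated tools and were checked by geriatricians and pharmacists of the team.

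The laboratory part of Table 2 has one thyroid row: "TSH < 0.34 μUI/L or fT4 > 12 μg/dL". No other part of the article gives a different thyroid unit or limit.

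On where the laboratory limits come from, the same section says: "We will also evaluate previously defined altered laboratory tests, according to reference laboratory and literature review". On what happens after an alert fires, it says: "All triggers will be further reviewed to discern if they are clearly independent from clinical manifestations related to the patients’ condition", and then "Causality will be then assessed using the 10-point Naranjo Scale". Severity and avoidability ratings and a blinded adjudication committee follow.

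**The concern.** A laboratory alert is a screening threshold. It is useful only if a patient with the abnormality can cross it. The TSH unit is per litre, where the number 0.34 makes sense per millilitre. The T4 limit is labelled free T4 but is of a size that belongs to total T4. If the row goes into the chart-review form as printed, a patient with drug-related thyroid excess, for example from too much replacement, would not be flagged by the only thyroid laboratory alert in the list.

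The later steps cannot repair this. The further review, the causality rating and the adjudication act only on alerts that have fired.

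**Working it through.** The article derives no figure here, so there is nothing of its own to reproduce. The check is unit conversion.

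**Inputs from Table 2:** TSH limit 0.34 μUI/L; free T4 limit 12 μg/dL.

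**Inputs that are assumptions, because the article gives none:** TSH assay detection limit 0.001 to 0.02 mUI/L; free T4 upper reference limit 1.5 to 2.0 ng/dL; molar mass of T4 about 777 g/mol.

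**TSH**

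- Conversion: 1 μUI/mL = 1 mUI/L = 1,000 μUI/L.
- Printed limit: 0.34 μUI/L ÷ 1,000 = 0.00034 mUI/L.
- Same number per millilitre: 0.34 μUI/mL = 340 μUI/L, and 340 ÷ 0.34 = 1,000. The printed limit is therefore 1,000-fold lower.
- Against the detection limit: 0.001 ÷ 0.00034 = 2.9, and 0.02 ÷ 0.00034 = 58.8. The printed limit lies about 3 to 59 times below what the assay is assumed to detect. The only results that could count as meeting it are those reported merely as below detection.

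**T4**

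- Conversion: 1 μg/dL = 1,000 ng/dL.
- Printed limit: 12 × 1,000 = 12,000 ng/dL.
- Against a free T4 upper limit: 12,000 ÷ 2.0 = 6,000, and 12,000 ÷ 1.5 = 8,000.

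**Does changing only the T4 unit repair the row?**

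| Reading of the number 12 | Equivalent | Result |
|---|---|---|
| Free T4, ng/dL | 12 ng/dL | 12 ÷ 2.0 = 6 to 12 ÷ 1.5 = 8 times the assumed upper limit |
| Free T4, pmol/L | 12 × 777 ÷ 1,000 ÷ 10 = 0.93 ng/dL | below the assumed upper limit, so ordinary results would exceed it |
| Total T4, μg/dL | 12 × 10 ÷ 777 × 1,000 = 154 nmol/L | the size of a total T4 limit |

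The TSH half has one evident repair, a change of unit. The T4 half does not. Keeping the free T4 label calls for a new unit and probably a new number; keeping the number and unit calls for a new label. Two reviewers who each correct the row in their heads could apply different rules.

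**The case against.** The strongest reply is that this is a one-row misprint of little consequence. Chart review is done by people, the article refers to laboratory reference values, and staff would probably read 0.34 in the unit on the laboratory report. Other alerts, such as delirium, falls or an unspecified adverse event, could still pick up a thyroid problem. Adverse drug events are secondary outcomes, and the Data analysis section treats all secondary analyses as exploratory.

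Most of that stands and limits the weight of the point. It does not make the row correct. Silent substitution is plausible for TSH but has no clear target for T4, and an unspecific alert is a chance finding rather than a replacement for the laboratory alert. Nor would a corrected row find everything: low TSH or high T4 marks thyroid excess, so the row would not detect the effect of stopping thyroid replacement.

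A reader might go further and infer that "Serum glucose >110 mg/dL" is broken too, because it looks mild beside "Serum glucose <50 mg/dL" and would flag nearly every chart. The article does not support that. It gives no glucose distribution, no number of readings and no fasting status. If a share p of independent readings exceeds the limit, the chance of at least one in k readings is 1 − (1 − p)^k. That is 10% with p = 0.10 and k = 1, but 99.6% with p = 0.50 and k = 8, so the result depends wholly on the assumption. A low limit is a sensitive, unspecific alert, not one that cannot work, and its hits go through review, causality rating and blinded adjudication. The absence of a baseline comparison does not single glucose out either, since potassium, sodium, INR and most other laboratory rows have none.

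A reader might also infer bias between phases, on the reasoning that the intervention lets glucose rise. Nothing in the article shows such a rise, and the same list and window apply in both phases.

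**Conclusion.** The thyroid row of Table 2 is wrong as printed and needs correction. The TSH limit is 1,000-fold too low by unit; this follows from arithmetic, on the reading that 0.34 was meant per millilitre. The T4 limit is thousands of times above any plausible free T4 result and fits total T4; this rests on the assumed reference limit, but a several-fold change in that limit would not alter the conclusion. Read literally, the alert would essentially never fire, apart from TSH results reported only as below detection.

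The consequence is minor. At risk is the detection of drug-related thyroid excess and the consistency of the chart review, within outcomes that the plan calls exploratory. The article gives no frequency of thyroid drug use, so the number of missed events cannot be estimated. The primary outcome, the sample size and the power are unaffected. For glucose, the documents support no more than checking that limit against the source tools.

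**What to change.** 1. Reconcile the thyroid row with the source trigger tools and with the hospital laboratory's assays and reporting units.
2. Correct the TSH unit to μUI/mL (equivalently mUI/L).
3. Restate the T4 part so that analyte, unit and limit agree: either free T4 with a unit and limit that fit that assay, or total T4 if that is what the source tool uses.
4. Carry the correction into the chart-review form. If charts have already been screened with the printed row, re-screen their thyroid results in both phases.
5. While the sources are open, confirm the upper glucose limit against them.

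The cost is one corrected table row, one change to the form and, if review has begun, a second look at the thyroid results. No change to the design, sample size or analysis is needed.

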### Outcomes

The primary outcome of the study is the mean number of medications per patient.

Secondary outcomes are (see also “Participant timeline and data collection”): prevalence of quantitative polypharmacy and hyperpolypharmacy, qualitative polypharmacy, PIMs, anticholinergic burden, number of underprescribed medications that have been started, ADEs and adverse drug withdrawal events (ADWEs), unplanned care utilization, and mortality. Patient-reported outcome measures (PROMs) will also be secondary outcomes for this study. They include adherence, treatment burden, perceived health status and quality of life, health literacy, and attitudes on deprescription (see Table 1). Finally, another secondary outcome will be the identification of barriers and facilitators of the implementation of the purposed methodology, both at the level of the individual person/healthcare professionals (possible cultural aspects, preferences, etc.) as well as from the system point of view (aspects related to intermediate care).

**Table 1 tab1:** Detailed collected variables.

Demographic variables	Multidimensional assessment	Medication assessment	PROMs

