### Data analysis

Baseline variables will be described using means and standard deviations for quantitative variables and absolute and relative frequencies for categorical variables, with their corresponding 95% confidence intervals. The Student’s t-test will be used to compare means of medications and other qualitative variables, and the chi-squared test will be used to compare polypharmacy, hyperpolypharmacy, ADEs, ADWEs, and other categorical variables. All analyses will be stratified according to frailty and to age groups, as appropriate.

We will perform a generalized lineal model with mixed effects for (individual) time and cluster. In the descriptive analysis we also will perform descriptions for each cluster. The ICC for within-cluster correlation will be analyzed and recalculated with the data result and included in a sensitivity analysis.

Multivariable analyses will be carried out to assess the association between decrease in the number of medications at discharge and possible determinants. PROMs will be assessed by comparison of scores before and after the intervention by using paired t-test for continuous variables and McNemar’s test for categorical variables. Cox proportional hazard models will be used to evaluate the association between intervention and survival or time to first unplanned health care utilization. Missing data will be handled according to multivariate imputations by chained equations. Interim analyses are not planned.

All the analysis of secondary outcomes will only be exploratory as far as the sample size is not powered to detect differences on these variables.

All analyses will be carried out according to the intention-to-treat principle, with statistical significance at *p* < 0.05. STATA and R-Studio software will be used in their most recent versions available for statistical analysis.

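### The trigger check for independence from the patient's condition may screen out relapse-type withdrawal events before blinded adjudication

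*Protocol article*

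**What the plan says.** The Outcomes section lists "ADEs and adverse drug withdrawal events (ADWEs") among the secondary outcomes. The procedure for finding them is in Participant timeline and data collection:

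- **Identification.** In both phases, "ADEs/ADWEs will be identified by research staff based on a retrospective review of medical records", from enrolment to index discharge or 30 days, whichever is earlier, using the alerts in Table 2. One of these alerts is "Abrupt medication stop".
- **Capture.** Alert diagnoses are unexpected manifestations during the admission that "might be related or unrelated to the use (or lack of use) of a certain medication".
- **Check.** "All triggers will be further reviewed to discern if they are clearly independent from clinical manifestations related to the patients"; the last word of that sentence is condition.
- **Causality.** "Causality will be then assessed using the 10-point Naranjo Scale". Severity and avoidability are also rated.
- **Adjudication.** "Each potential ADE/ADWE form will be evaluated by the blinded members of the ADE/ADWE Adjudication Committee", a geriatrician and a clinical pharmacist who are not directly involved in the retrospective review.

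The Data analysis section compares ADEs and ADWEs with a chi-squared test and adds that "All the analysis of secondary outcomes will only be exploratory".

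**The concern.** The check is built for drug toxicity. It asks whether an event can be told apart from the patient's own illness, which is a sensible question when a drug is suspected of causing harm. For a withdrawal event in which the treated disease comes back, the question points the wrong way: the event is the patient's illness, and the link to medication is that a drug was stopped.

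The intervention aims to reduce the number of drugs, so withdrawal events are the harm most directly tied to it. If relapse-type events are taken out at this step, the comparison of ADWEs between phases understates that harm, and a committee that works from forms cannot restore events for which no form is made. The Discussion presents the ADE/ADWE data as information on the model's safety, so readers will use the comparison in that way even though it is exploratory.

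**Working it through.** The protocol gives no ADE or ADWE rate and no power figure for these outcomes, so there is no figure to reproduce. The check is a reading of the steps in order.

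**1. Is lack of use within scope?** Yes. The capture sentence names it, ADWEs are a secondary outcome, and the forms and the committee both carry ADWE in their names.

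**2. Does the independence check apply to withdrawal triggers?** Yes. It covers all triggers and makes no exception. A Table 2 alert for an abrupt stop passes through the same check.

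**3. Can return of disease meet the criterion?** Take a patient whose drug for a condition is stopped after enrolment and whose condition then recurs. The recurrence is a manifestation of that condition, so it is not independent of it. A withdrawal reaction that is not a sign of the underlying disease could still pass. The problem is therefore confined to relapse-type ADWEs.

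**4. Does the check act before the committee?** This is not written. The text does not say that a trigger failing the check is dropped, who makes the check, or whether every trigger produces a form. Four features point to a filter ahead of the committee:
- The check is described first, and causality is assessed then.
- A sorting step with no consequence would have no purpose.
- The committee receives forms for potential events, not triggers.
- Its members stand outside the retrospective review, and research staff do the identification.

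**5. Is the check blinded?** Blinding is stated only for the committee, and the Design section describes the trial as open-label. The check may therefore be made with the phase known.

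**6. In which direction would the error go?** Let p1 and p0 be the true ADWE risks in the intervention and control phases, s the relapse-type share, and f the fraction of those events removed. If s and f are the same in both phases:

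reported difference = p1(1 − s·f) − p0(1 − s·f) = (p1 − p0)(1 − s·f)

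The events lost per patient are p1·s·f and p0·s·f, so more are lost in the phase with the higher risk. The Sample size section expects a decrease of 1.31 drugs from a baseline mean of 8.81, which makes p1 > p0 plausible. The reported excess would then shrink towards zero. The ratio p1/p0 would be unchanged while f is equal in both phases. If the check is unblinded, f need not be equal. None of p1, p0, s or f is in the document, so the formula gives a direction under stated conditions and no size.

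**The case against.** **No discard rule is written.** A reader might infer that the protocol orders relapse events to be removed before the committee sees them. It does not. It says that triggers are reviewed to discern something and leaves the consequence open. This objection stands, and the point is therefore put as a risk created by the wording.

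**There are not two rival definitions of the event.** A wide capture followed by review is ordinary trigger methodology, and the article never says whether relapse after stopping counts as an ADWE. That also stands. What remains is that the review criterion does not suit one kind of event that the capture step lets in.

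**A narrower reading is possible.** Patients mostly arrive after hip fracture, stroke or an acute stay, and the patient's condition could mean that illness only. The intent to keep withdrawal events is clear from the terms used. But the sentence does not limit itself in this way, and two reviewers could class the same relapse in opposite ways.

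**Loss may not be confined to ADWEs.** Delirium, falls or hypotension in a frail inpatient are also seldom plainly separate from the patient's condition, so a strict check could remove ADEs too. This stands: a reader might infer that the filter spares drug toxicity and removes only withdrawal harm, but the documents do not show that. Controls also have a pharmacist review that can stop drugs, so ADWEs in the control phase could be lost as well.

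**Other data cover the gap.** Acute admissions, emergency visits and deaths are collected to 90 days after discharge with no such check stated. Serious relapses may appear there, but they are not labelled as ADWEs and do not restore the ADWE count.

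**This is procedural detail left to the full protocol.** Who reviews and how failures are recorded may well be in a fuller document. The criterion itself, however, is stated in the article and applied to all triggers.

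**Conclusion.** The point holds as a probable under-count, not as a demonstrated one. As worded, the independence check cannot be met by return of a disease after its drug is stopped, although events from lack of use and ADWEs are meant to be captured. The conclusion that such events may be lost before blinded review rests on two assumptions that the order of the steps supports but the text does not state: that a trigger failing the check is dropped, and that this happens before a form reaches the committee.

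That the loss would be larger in the intervention phase rests on a third assumption, that more drugs are stopped there, which is the purpose of the intervention. A reader might want a figure for the bias; none can be given, because the document has no ADWE rate, relapse share or removal fraction. The consequence is limited to an exploratory secondary safety comparison. The primary outcome, the sample size and the 75% power are not affected. The correction is worth making because it is small and the outcome is the one most directly exposed to the harm of stopping drugs.

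**What to change.** Add one sentence to the adjudication procedure, for both phases: relation to the patient's underlying condition is not a ground for screening out a trigger that follows a stop or dose reduction of any drug since enrolment. Send such triggers to the existing blinded committee as potential ADWEs, for it to accept or reject. Report by phase the number of triggers screened out and the number forwarded.

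The wording says any drug, so that staff who may know the phase need not judge whether the drug was used for the condition that returned. If more drugs are stopped in the intervention phase, more of its triggers will be forwarded. Final acceptance still rests with the blinded committee, and the reported counts let a reader see any difference in ascertainment.

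The cost is some extra forms for the committee; how many cannot be said from the document, and several Table 2 alerts are broad. No new staff or patient contact is needed. The change concerns event classification only and alters nothing in patients' treatment.

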### Data analysis

Baseline variables will be described using means and standard deviations for quantitative variables and absolute and relative frequencies for categorical variables, with their corresponding 95% confidence intervals. The Student’s t-test will be used to compare means of medications and other qualitative variables, and the chi-squared test will be used to compare polypharmacy, hyperpolypharmacy, ADEs, ADWEs, and other categorical variables. All analyses will be stratified according to frailty and to age groups, as appropriate.

We will perform a generalized lineal model with mixed effects for (individual) time and cluster. In the descriptive analysis we also will perform descriptions for each cluster. The ICC for within-cluster correlation will be analyzed and recalculated with the data result and included in a sensitivity analysis.

Multivariable analyses will be carried out to assess the association between decrease in the number of medications at discharge and possible determinants. PROMs will be assessed by comparison of scores before and after the intervention by using paired t-test for continuous variables and McNemar’s test for categorical variables. Cox proportional hazard models will be used to evaluate the association between intervention and survival or time to first unplanned health care utilization. Missing data will be handled according to multivariate imputations by chained equations. Interim analyses are not planned.

All the analysis of secondary outcomes will only be exploratory as far as the sample size is not powered to detect differences on these variables.

All analyses will be carried out according to the intention-to-treat principle, with statistical significance at *p* < 0.05. STATA and R-Studio software will be used in their most recent versions available for statistical analysis.

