## Description of the methodology

### Design

This study will follow a type 2 hybrid design (26) to implement and evaluate a complex intervention, using mixed methods. In detail, we will conduct a single centre, pragmatic, stepped-wedge randomized cluster open-label trial design (27). The units of randomization will be five geriatric rehabilitation units of the ICH (5 clusters). The unit of analysis will be the patient.

All clusters (hospital wards) will begin the study under the control condition. Subsequently, they will be randomly assigned to the intervention at predetermined time points in a sequential, staggered manner until all clusters receive the intervention (see Figure 1).

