**Figure 1 fig1:**
[figure not shown]
Stepped-wedge trial design. C, cluster; 0, control; 1, intervention. Each square includes 10 patients.

The computer-generated stepwise randomization of clusters will be carried out with the statistical software R with a randomization seed 184.

For the identification of barriers and enablers for the implementation, we will follow qualitative analysis combining techniques of semi-structured interviews and focal groups.

Trial registration (clinical trial number): NCT07015112 (June 10, 2025).

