### Sample size and recruitment

Sample size was calculated using the Stata command stepped-wedge, considering 5 clusters, a size of each cluster *N* = 10 and five times of measurement after baseline, incorporating one cluster to the intervention phase at each time. Based on previous studies (21), taking a baseline mean drugs of 8.81 and expected decrease of 1.31, we considered an ICC = 0.2 (intraclass correlation). With this data, a sample size of 300 subjects will provide a power of 75%. The sample size was calculated by a statistician within the research group.

For the qualitative part, we aim to recruit and interview 15 older patients with different frailty profiles (mild, moderate, and severe frailty), from both genders. Caregivers of those patients, especially the most severely frail, and 5 geriatricians will also be invited to join the study. We estimate a total of 20–30 participants in this group. Additionally, we aim to include a minimum of 4 focal participation groups (between 5 and 10 people per group), including both patients and healthcare professionals (geriatricians, pharmacists and nurses). The selection of the group participants will be performed to obtain a balanced representation of the different profiles.

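### Unadjusted t-tests and chi-squared tests are named for between-condition comparisons in a five-ward stepped wedge, and the mixed model that is also planned is not made the primary analysis

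*Protocol article*

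**What the plan says.** The Design section describes a stepped wedge: "The units of randomization will be five geriatric rehabilitation units of the ICH (5 clusters". Sample size and recruitment adds "five times of measurement after baseline, incorporating one cluster to the intervention phase at each time", the Figure 1 caption says "Each square includes 10 patients", and for the clustering "we considered an ICC = 0.2 (intraclass correlation". The Outcomes section makes the mean medication count per patient the primary outcome.

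Data analysis then names these methods:

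- Student's "t-test will be used to compare means of medications and other qualitative variables" (the last words look like a slip for quantitative variables).
- "the chi-squared test will be used to compare polypharmacy, hyperpolypharmacy, ADEs, ADWEs, and other categorical variables".
- "We will perform a generalized lineal model with mixed effects for (individual) time and cluster".

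The section sets significance at p < 0.05 for all analyses and labels every analysis of secondary outcomes exploratory. It does not say whether the t-test or the mixed model decides the primary outcome.

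**The concern.** In a stepped wedge the two conditions are not exchangeable groups of patients. Wards that cross early supply most of the intervention patients, wards that cross late supply most of the controls, and intervention patients come later in calendar time by construction. A pooled two-group test therefore mixes the intervention effect with differences between wards and with any change in prescribing over time. It also uses a standard error that treats patients in the same ward as independent.

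The t-test is the only method tied by name to medication counts, and the trial was sized on the premise that those counts are correlated within wards. At stake is whether a p-value below 0.05 on the primary outcome would mean anything, and whether two analyses with very different error rates are both left available for it.

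**Working it through.** **Inputs.** Five wards (Design); six periods, that is baseline plus five, with one ward crossing at each step, and ICC 0.2 (Sample size and recruitment); 10 patients per cell (Figure 1 caption); significance level 0.05 (Data analysis), taken as two-sided, which is an assumption.

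**The plan's own figures.** 5 × 6 × 10 = 300, which matches. The stated 75% power cannot be reproduced because no SD is given. Under the standard stepped-wedge variance formula with a decrease of 1.31 and ICC 0.2, 75% power corresponds to a total SD of about 2.74 drugs. The false-positive rates below do not depend on this SD.

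**Layout.** Intervention patients per ward are 50, 40, 30, 20, 10 and controls are 10, 20, 30, 40, 50, so 150 in each condition.

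**Variance of the pooled difference in means** (total variance 1, no intervention or period effect):

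- Ward weights: (40, 20, 0, −20, −40)/150; sum of squares 4000/22500 = 0.1778.
- True variance: 0.2 × 0.1778 + 0.8 × 2/150 = 0.0356 + 0.0107 = 0.0462.
- Variance that the t-test assumes: 2/150 = 0.0133.
- Ratio: 0.0462/0.0133 = 3.47; square root 1.862.
- False-positive rate: 2 × [1 − Φ(1.96/1.862)] = 29.2%.

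Simulating 20,000 trials and applying the t-test gives 30.1%. If the ward effect drifts between periods (cluster autocorrelation 0.8), the simulated rate is 29.0%.

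| ICC | Formula | Simulation |
|---|---|---|
| 0.01 | 6.4% | 6.6% |
| 0.05 | 12.3% | 11.7% |
| 0.10 | 19.0% | 19.5% |
| 0.20 | 29.2% | 30.1% |

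**Calendar time.** Numbering periods 1 to 6 and counting ward-periods, the mean period is (1×2 + 2×3 + 3×4 + 4×5 + 5×6)/15 = 70/15 = 4.67 for intervention patients and (5×1 + 4×2 + 3×3 + 2×4 + 1×5)/15 = 35/15 = 2.33 for controls. The gap is 2.33 periods. The documents give no secular trend, so these drifts are assumptions:

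| Drift per period | Bias (2.33 × drift) | In drugs at SD 2.74 | t-test false positives, ICC 0.2 |
|---|---|---|---|
| 0 | 0 | 0 | about 30% |
| 0.05 SD | 0.117 SD | 0.32 | about 37% |
| 0.10 SD | 0.233 SD | 0.64 | 53% to 54% |

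A bias of 0.64 drugs would be 0.64/1.31 = 49% of the planned effect.

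**Comparator.** Least squares with an intervention indicator and ward and period effects rejects in 5.2%, 5.2% and 5.1% of 20,000 simulated trials at drifts of 0, 0.05 and 0.10 SD. Wards were fixed effects here and constant over time. A random-effect version with only five wards needs a small-sample correction and should not be assumed to hold 5% without one.

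**What the named tests cover.** The paragraph opens with baseline description, but Participant timeline and data collection has adverse drug events and withdrawal events recorded from enrolment to discharge or 30 days. They cannot be baseline variables, so the paragraph covers outcome comparisons.

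**The case against.** The strongest reply is that the plan already contains a model with time and cluster, so the 30% is the error of a test to which nobody has given the deciding role. This stands in part. A reader might infer that the trial has no analysis that respects its design, or that the t-test will decide it; the document supports neither. What remains is that the model sentence names no outcome and no intervention term and claims no priority, and that its qualified reference to time could mean a patient's own follow-up time rather than calendar period.

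A second reply is that the tests are descriptive. For medication counts that reading is partly open. For adverse drug events it is not, because of when they are collected.

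Third, polypharmacy and adverse events are secondary and declared exploratory, and no ICC is given for them. This stands: the 30% must not be carried over to the chi-squared tests. The exploratory label limits the consequence, but it does not remove the confounding with ward and calendar time.

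Fourth, a reader might extend the point to the survival analyses, where "Cox proportional hazard models will be used to evaluate the association between intervention and survival or time to first unplanned health care utilization" with no mention of ward or period. That sentence lists no covariates at all. Silence in a condensed article is not an exclusion, and no error rate was computed for these models, so this is not counted as an error.

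That a statistical analysis plan may add detail is no answer to the core point. The protocol itself names a test for the primary outcome that conflicts with the ICC used to size the trial.

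**Conclusion.** The point holds in a limited form. The Data analysis section names unadjusted tests for between-condition comparisons in a five-ward stepped wedge and does not say that the mixed model takes precedence. If the t-test decided the primary outcome, the false-positive rate would be about 30% at ICC 0.2 with no secular trend. That figure rests on the planned layout, a two-sided 5% level and the planning ICC; it falls to about 12% at ICC 0.05 and 6% to 7% at ICC 0.01. The drift results are illustrations on assumed trends, and their conversion to drugs uses an SD implied by the stated power. Neither is a prediction for this hospital. The error rate applies to medication counts only; the confounding with ward and calendar time applies to the binary outcomes as well. Because the primary outcome is affected, the wording should be settled before any between-condition analysis.

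**What to change.** In Data analysis:

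1. Name the mixed model as the primary analysis of medication count, with an intervention indicator, calendar period as a six-level fixed effect, a ward random effect, and a small-sample correction suited to five wards, such as Kenward-Roger.
2. Use the same structure with a suitable link for polypharmacy, hyperpolypharmacy, adverse drug events and withdrawal events, keeping their exploratory label.
3. State that t-tests and chi-squared tests are descriptive only. They need not be removed.
4. Optionally, say that ward and period will also be accounted for in the Cox models. This is a clarification, not a correction.

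The cost is wording. No new data or patients are needed. The small-sample correction makes intervals slightly wider than an uncorrected mixed model would, and may take power a little below the stated 75%; that loss was not computed.
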